### Statistical analysis

We will describe the demographics of the study population, such as age and sex distribution, medical history and prescribed medication, using means and SDs for continuous variables, and frequencies and proportions for categorical variables. For each analysis, we will use conditional logistic regression to estimate IRRs, with 95% CIs, for the risk of acute MI or stroke in prerisk and risk periods compared with baseline periods. We will include only individuals who have experienced both the outcome and the exposure, and will include only the first acute MI or stroke diagnosis in the observation period. The IRRs will be adjusted for time-varying confounders: age, season and year of UTI diagnosis. Year of UTI diagnosis is included because diagnostic and coding practices may have changed over time as a result of guidance and awareness around microbial resistance. Adjusted IRRs will be reported for the risk of acute MI or stroke at 1–7, 8–14, 15–28 and 29–90 days after UTI. We will conduct the analysis in R, using the SCCS package. We will report the findings in accordance with REporting of studies Conducted using Observational Routinely-collected Data (RECORD) and STrengthening the Reporting of OBservational studies in Epidemiology (STROBE) guidelines.

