### Study design

Individuals who experience UTIs and individuals who do not can differ in unmeasured ways and hence could be sources of residual confounding. We will use the SCCS design method to deal with this issue. The SCCS method is an epidemiological study design for which individuals act as their own control so that both measured and unmeasured characteristics that vary between individuals are completely controlled.^27^ Only individuals who have experienced an outcome and exposure of interest are included. The SCCS method compares the incidence of an outcome during predefined risk periods with incidence during baseline periods (all times outside of risk and prerisk periods) and estimates the temporal association between a transient exposure and outcome. Time-invariant covariates (eg, sex) are inherently controlled for, and time varying covariates (eg, age) are adjusted for within the models. The method was originally developed to investigate associations between vaccinations and acute adverse events, such as aseptic meningitis,^28 29^ but has since been applied in a range of epidemiological settings,^30–32^ including non-acute events such as autism.^33^ As with other study designs, the SCCS method makes several assumptions that need to be met in order to obtain valid and unbiased estimates, but there are model extensions which provide solutions to violations of these assumptions under certain circumstances.^34^ The model assumptions, how they apply to our study, and the solutions to violations of the assumptions are given in table 1.

**Table 1 T1:** Model assumptions and solutions to violations of those assumptions

Assumption	How the assumption applies to this study	Solution	Example of use of the solution in the literature
Subsequent exposures should not be affected by previous events.	We might see a temporary increase in UTIs subsequent to an MI or stroke event, which would bias estimates towards the null.	Apply a prerisk period.	Gibson *et al* studied the association between prescription drugs and road traffic accidents. As some drugs may be used to treat anxiety or pain caused by the crash, a 4-week pre-exposure period was included.^37^

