	As both MI and stroke have relatively high death rates, the length of the observation period is dependent on events, and no further exposures are possible after death.	Use an event-dependent observation period model extension^38^ and conduct a sensitivity analysis that repeats the analysis, excluding individuals who died within 30 days of the event.	Bruer *et al* used the event-dependent observation period model extension in their study on the association between antipsychotic drugs and myocardial infarction.^39^ Langan *et al* studied the risk of stroke following herpes zoster. They conducted a sensitivity analysis excluding individuals who died within 90 days of stroke.^40^
Event rates are constant within defined periods	MI and stroke are more common in older individuals and may be affected by seasonal changes.	Control for age and season effects.	Grave *et al* studied the association between seasonal influenza vaccination and Guillain-Barré syndrome. They adjusted for calendar month, as the vaccinations are seasonal by design.^41^ In a study of the association between chickenpox and stroke, Thomas *et al* adjusted for age in 5-year age bands.^42^
Events are independently recurrent or rare.	MI and stroke are not independent: once an individual has a first event, they are more likely to have a second.	Study first events only.	Langan *et al* began the observation period 12 months into follow-up time to ensure first stroke events had been correctly identified.^40^

MI, myocardial infarction; UTIs, urinary tract infections.

A diagrammatic representation of observation time for an individual in the proposed SCCS design is given in figure 1. Risk periods start on the date of an UTI and end 90 days later. The date of an UTI is the earliest date of occurrence of any of the events necessary for each different UTI definition. For example, the definition of UTI in our primary analysis is a combination of an UTI-related diagnostic code and antibiotic prescription in WLGP data and a urine culture result that supports a diagnosis of UTI in the WRRS data, occurring within a 7-day window. In this case, the date of the UTI would be the date of whichever of the following events occurred first: UTI-related diagnostic code, antibiotic prescription, supporting urine culture.

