**Figure 1 F1:**
[figure not shown]
Diagrammatic representation of observation time for an individual in the proposed self-controlled case series design. MI, myocardial infarction; UTI, urinary tract infection.

Individuals can have more than one UTI during the observation period, and therefore can have more than one 90-day risk period. Where risk periods overlap, the later period takes precedence, and the earlier period is shortened. There will be a prerisk period of 7 days before the risk period, to allow for the situation where an individual has an UTI for several days prior to consultation, so events in the prerisk period are not erroneously attributed to the baseline period.

Baseline periods are all times outside of the risk and prerisk periods. The study period is from 1 January 2010 to 31 December 2020. The observation period is different for each individual. It generally follows the study period but may start later for some individuals who were not Welsh residents at the start of the study period but became so later, or who turned 30 years of age sometime during the study period. Similarly, the observation period may end before the study period when individuals moved out of Wales or died.

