### Sensitivity and subgroup analyses

We will perform several sensitivity and subgroup analyses to assess the robustness of the findings of our primary analysis to different assumptions:

We will explore the impact of using a wider definition of MI and stroke, including ICD-10 codes for acute coronary syndromes and transient ischaemic attacks. This will include events that have potentially been missed by our main definition and assess how sensitive our findings are to the definition of MI and stroke.We will explore the impact of widening the microbiological definition of UTI to bacterial growth of a single organism of ≥1x10^7^ CFU per litre irrespective of WCC.We will differentiate first-ever MI or stroke from recurrent events, and report risk estimates separately. This analysis will exclude individuals with a PEDW record of an event before the observation period, and include only those who have their first ever event during the observation period.We will extend the prerisk period to 14 days. Some individuals may have had an UTI for several days prior to diagnosis, and so an acute MI or stroke during this time may relate to exposure but without a prerisk period, would count towards the baseline period.We will repeat the analysis excluding individuals who died within 30 days of an event to examine the potential effect of an event dependent observation period.We will restrict the definition of UTI to include only antibiotic prescriptions for nitrofurantoin (currently recommended first-line therapy) to explore whether the choice of antibiotic impacts the findings.We will use interaction terms to assess the impact of specific bacterial organisms on the relationship between UTI and MI or stroke.We will examine whether the COVID-19 pandemic may affect our findings by (1) excluding individuals whose MI or stroke occurred in 2020, and (2) including an interaction term to explore whether the association between exposure and outcome differs in 2020 vs pre-2020.We will include an interaction term to explore whether the association between exposure and outcome differs in those with and without a history of diabetes, given its potential role as a risk factor of both UTI and MI/stroke.

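### Year of UTI diagnosis cannot act as a confounder in the self-controlled model: use calendar year of the observation interval, and say when observation ends in the 2020 exclusion analysis

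*Protocol article*

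**What the plan says.** The Statistical analysis section of the protocol article fixes the adjustment set: "The IRRs will be adjusted for time-varying confounders: age, season and year of UTI diagnosis". It then gives a reason for the last term: "Year of UTI diagnosis is included because diagnostic and coding practices may have changed over time". Table 1, under Study design, answers the assumption of constant event rates with "Control for age and season effects". Calendar year of observation time is not named as a covariate anywhere.

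The Study design section sets out what the model can adjust for: "Time-invariant covariates (eg, sex) are inherently controlled for, and time varying covariates (eg, age) are adjusted for within the models". Below Figure 1 it allows repeat exposures: "Individuals can have more than one UTI during the observation period". The analysis set is exposed cases only: "We will include only individuals who have experienced both the outcome and the exposure".

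Under Sensitivity and subgroup analyses, the pandemic is handled in two ways. Analysis (1) works by "excluding individuals whose MI or stroke occurred in 2020"; analysis (2) by "including an interaction term to explore whether the association between exposure and outcome differs in 2020 vs pre-2020". The only reasons given for observation ending before the study period does are leaving Wales and death (Study design, below Figure 1).

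**The concern.** A covariate can control confounding in a self-controlled model only if it changes over a person's own follow-up. The year in which a UTI was diagnosed does not: it belongs to the episode. The plan nevertheless lists it as a time-varying confounder and gives it a job to do. If it is fitted as written, the report will claim an adjustment that was not made.

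The COVID-19 exclusion raises a related question about calendar time. Removing people by the date of their event, without shortening anyone else's observation, leaves 2020 person-time in which no event can occur by construction. A check meant to show whether 2020 matters could then move for a reason unrelated to the pandemic.

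**Working it through.** **1. The plan's own figure.** The article gives no number for calendar adjustment. The nearest is 90% power for an IRR of 1.3 (Sample size and power). For MI, exposed cases are 0.10 × 51 656 = 5166, and mean observation is 0.628 × 3251 + 0.372 × 2981 ≈ 3151 days. With r = 90/3151, the signed-root likelihood-ratio formula for a self-controlled series without age effects needs 4813 exposed cases and gives 91.9% power. The observation length used is not stated; other choices give 84.9% (MI, 4018 days) to 95.9% (stroke, 2887 days). The formula contains no calendar term, so nothing below changes it.

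**2. Why the covariate drops out.** For person i with one event, in interval k of length e, the likelihood contribution is

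e_ik·exp(βx_ik + α_age(ik) + γz_i) / Σ_m e_im·exp(βx_im + α_age(im) + γz_i).

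If z_i is the year of that person's only UTI, exp(γz_i) is a common factor and cancels, so γ has zero information. With several UTIs, z has no defined value in baseline intervals. If z is coded only inside risk windows, it becomes exposure × year, which is effect modification.

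**3. What age already does.** Within a person, age = t − b_i, where b_i is the birth date. A log-linear calendar trend is exp(δt) = exp(δb_i)·exp(δ·age). The first factor cancels and the second adds to the age slope. With an assumed age slope of 0.06 and δ = −0.03, the model sees a slope of 0.06 − 0.03 = 0.03 and needs no calendar term.

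**4. Size in the main model.** Large-sample fit of the conditional model: 132 monthly intervals, one UTI per person, 3-month risk window, true IRR 1.3, outcome rate rising 6% per year of age. The trends are assumptions, because the documents give none.

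| Assumed scenario | No age term | 5-year age bands | Bands + year of UTI | Linear age | Bands + interval calendar year |
|---|---|---|---|---|---|
| UTI +10%/yr, outcome −3%/yr | 1.340 | 1.306 | 1.306 | 1.300 | 1.301 |
| UTI +10%/yr, outcome −5%/yr | 1.316 | 1.303 | 1.303 | 1.300 | 1.300 |
| UTI +5%/yr, outcome −3%/yr | 1.319 | 1.303 | 1.303 | 1.300 | 1.300 |
| 2020: outcome ×0.8, UTI ×0.7 | 1.292 | 1.300 | 1.300 | 1.304 | 1.300 |
| 2020: outcome ×0.8, UTI ×0.5 | 1.298 | 1.309 | 1.309 | 1.311 | 1.299 |
| Mid-study step: outcome −0.15 (log scale), UTI ×1.5 | 1.326 | 1.302 | 1.302 | 1.295 | 1.301 |

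Year of UTI changes nothing in any row. With age in the model, the largest departure is 1.311/1.3, or +0.9%.

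**5. The 2020 exclusion, read literally.** Same model with 5-year age bands and no calendar trend; recorded UTIs in 2020 are multiplied by the factor shown.

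| UTIs in 2020 | 2020 cases dropped, others' 2020 time kept | Observation ended 31 December 2019 | Shift |
|---|---|---|---|
| ×1 | 1.312 | 1.301 | +0.8% |
| ×0.7 | 1.342 | 1.300 | +3.2% |
| ×0.5 | 1.357 | 1.301 | +4.3% |
| ×1.5 | 1.249 | 1.302 | −4.0% |

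Fewer UTIs in 2020 make the event-free time mostly baseline time, which lowers the baseline rate and raises the IRR; more UTIs do the reverse. Age bands cannot absorb a rate that falls to zero in one year.

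These runs follow everyone for all 11 years. The article reports mean observation of 2796 to 3251 days by outcome and sex, so many cases have no 2020 time. With an assumed follow-up mix averaging about 3105 days, the results are 1.317 (×0.5), 1.311 (×0.7) and 1.287 (×1.5): shifts from 1.3 of +1.3%, +0.8% and −1.0%.

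**The case against.** The best defence is that the harm is slight. A reader might infer from the useless covariate that secular trends in admissions and in UTI recording pass straight into the IRR. A calculation with calendar trends alone (events falling 3% to 5% a year, recorded UTIs rising 5% to 10%) would suggest a bias of −1.5% to −5%. The documents do not support that reading: the calculation leaves out age, and the plan adjusts for age and season. Once age is in the model, the residual for those same trends is at most +0.5%, with the opposite sign. This part of the defence stands.

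It may also be said that the authors meant calendar year of follow-up. If the analysts code it so, only the wording is at fault. But the sentence giving the reason repeats the term and ties it to how UTIs are diagnosed and coded, so the text does not show that intention.

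On the 2020 exclusion, a reader might take it as settled that 2020 time stays in the denominator. The article does not say so. It states no end date for this analysis, a condensed article may leave that to the full plan, and the problem disappears if observation stops at the end of 2019. The point is therefore conditional and concerns one sensitivity analysis.

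Finally, calendar year is nearly collinear with age within a person, so adding it recovers only the non-linear part. That is true, and it is the part still missing.

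**Conclusion.** The adjustment is wrong as written. Year of UTI diagnosis carries no information as a main effect and cannot do the job the article gives it. That conclusion is algebraic and rests on no assumed figure.

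The consequence for the main IRR is small: less than about 1% in every age-adjusted scenario tried, arising only from calendar effects that age cannot mimic. The literal 2020 exclusion could move its own sensitivity IRR by roughly 1% to 4% in either direction. The upper end needs full 11-year follow-up and a large change in recorded UTIs in 2020; shorter follow-up brings it to about 1%.

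These sizes depend on the assumed age slope, trends and 2020 factors. Neither point alters the design, the stated power or the likely primary conclusion. This is a specification to correct before analysis, not a critical flaw.

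**What to change.** In the adjustment set, replace year of UTI diagnosis with calendar year of each observation interval, entered as a time-varying factor alongside age band and season, and bring Table 1 into line. State that, because age and calendar time move together within a person, this term captures only non-linear calendar effects. If changing diagnosis and coding is itself of interest, fit UTI period × exposure as a separate effect-modification analysis and label it so.

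For COVID-19 analysis (1), state that everyone's observation ends on 31 December 2019, rather than only excluding people by event year. The calendar-year factor also supplies the 2020 main effect that the interaction in analysis (2) needs and that the stated adjustment set does not list.

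The cost is about ten extra parameters (11 calendar years, one as reference) against some 5000 or more exposed cases per outcome at the plan's 10% exposure rate, and one stated end date.

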## Methods and analysis

### Aims and objectives

The specific objectives of this research are to:

Estimate incidence rate ratios (IRRs) for acute MI and stroke in the 90 days following a clinically suspected and microbiologically confirmed UTI compared with baseline (all times outside of the 90-day risk period).Assess the effect of different methods of UTI ascertainment on estimated rate ratios (ie, clinically suspected and microbiologically confirmed; clinically diagnosed only; clinically suspected but not supported by microbiology and UTI diagnosed and treated in hospital).Investigate whether the effect of a clinically suspected and microbiologically confirmed UTI on acute MI and stroke differs according to the infecting organism.

Our primary hypothesis is that a clinically suspected and microbiologically confirmed UTI will increase the risk of acute MI or stroke in the 0–90 days postinfection period.

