### Exposure

The exposure of interest is an UTI. The risk period is 0–90 days following an UTI. This period was chosen as previous research has shown an increase in acute MI and stroke risk in the 1–90 days following an UTI.^6^ There will be a prerisk period of 7 days before the risk period, to allow for the situation where an individual has an UTI for several days prior to consultation, so events in this period are not erroneously attributed to the baseline period. Individuals can be exposed to an UTI more than once during the observation period. Each exposure will be followed by the same 90-day risk period. Baseline periods are all other times.

To ascertain UTI, we developed definitions that reflected the Public Health Wales Microbiology Division’s standard operating procedure for the investigation of urine.^36^ These procedures are followed by NHS microbiology laboratories across Wales. For each definition, the data sources required and the clinical scenario represented is summarised in table 2, and the code lists used are given in online supplemental material B–D. In our primary analysis, an individual will be regarded as being exposed to an UTI if the following events occur within a 7-day window:

A General Practice (GP) record of an UTI diagnostic or symptom code.A GP record of an antibiotic prescription.A microbiology record of a urine sample with bacterial growth of a single organism of ≥1x10^8^ colony-forming units (CFU) per litre and white cell count (WCC)≥1x10^8^/L. If there are two organisms grown, both must demonstrate growth of ≥1x10^8^ CFU per litre. More than two organisms will be regarded as mixed growth and thus not supportive of an UTI diagnosis. In a sensitivity analysis, we will widen the microbiological criteria and include all urine samples with bacterial growth of a single organism of ≥1x10^7^ CFU per litre, irrespective of the WCC.

**Table 2 T2:** Definitions of UTI for primary and secondary analyses. As the UTI definitions are combinations of two or more components, the start of the risk period is defined as the date of the earliest component

	UTI-related read code in GP data (online supplemental material B)	Antibiotic prescription in GP data (online supplemental material C)	UTI-related ICD-10 code in PEDW (online supplemental material D)	Urine culture results in WRRS	Time frame	Clinical scenario

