### Sample size and power

Our initial work has identified 51 656 individuals with acute MI and 58 146 with stroke in the SAIL Databank who meet all inclusion criteria. In the previous study by Smeeth *et al*,^6^ the sample size was 53 709 for acute MI, and 55 157 for stroke, where 16% of acute MI cases, and 21% of stroke cases were exposed to UTI.^6^ Based on a conservative exposure rate of 10%, and an at-risk window of 90 days, we estimated the effect size that could be reliably detected with our potential sample size, using the sample size function in the SCCS package in R. The available sample provides 90% power to detect an IRR of 1.3 at the alpha=0.05 level, which is smaller than the IRRs detected in Smeeth *et al*^6^

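### The hypothesis and power figure concern one 0–90-day rate ratio, but the listed results are four sub-windows from day 1, with no primary contrast named and no window for day 0

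*Protocol article*

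**What the plan says.** **Hypothesis and objective.** Under Aims and objectives, the primary hypothesis is that a confirmed UTI "will increase the risk of acute MI or stroke in the 0–90 days postinfection period". Objective 1 seeks the IRRs for MI and for stroke over the 90 days after a confirmed UTI. Its comparator is worded "compared with baseline (all times outside of the 90-day risk period").

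**Risk and prerisk periods.** Study design: "Risk periods start on the date of an UTI and end 90 days later". Exposure: "The risk period is 0–90 days following an UTI", and "There will be a prerisk period of 7 days before the risk period". Study design defines baseline twice, both times as time outside the risk and the prerisk periods.

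**Power.** Sample size and power assumes 10% exposed and "an at-risk window of 90 days", and claims 90% power for an IRR of 1.3 at alpha 0.05.

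**Analysis.** Statistical analysis first says in general terms that IRRs with 95% confidence intervals will be estimated for prerisk and risk periods against baseline. It then gives the specific results: "Adjusted IRRs will be reported for the risk of acute MI or stroke at 1–7, 8–14, 15–28 and 29–90 days after UTI".

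**The concern.** Three statements in the same article do not fit together.

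1. **Primary contrast.** The hypothesis and the power figure belong to one 90-day contrast, while the listed results are four shorter ones for each of MI and stroke. Nothing says which contrast decides. If a short window is raised and the overall IRR is near 1, or the reverse, the reading could be chosen after the results are seen. The article says that an association would support a funding application for a randomised trial, so the reading matters.
2. **Day 0.** The UTI date belongs to the risk period, but the windows start at day 1 and the prerisk period ends before day 0. Same-day events are the ones most open to reverse causation, and the article itself worries that early cardiovascular symptoms may be labelled as UTI. In secondary analyses 4 and 5 a UTI can be identified from hospital coding, the same source as the outcome. One admission could then carry both codes; whether they would share a date is not stated.
3. **Baseline.** Objective 1 leaves the prerisk days in baseline; Study design takes them out.

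**Working it through.** **Inputs from the article**
- Cases: 51 656 MI and 58 146 stroke. With 10% exposed: n = 5165.6 and 5814.6.
- Mean observation (Summary of cases), weighted by the sex split in table 3. MI: 0.628 × 3251 + 0.372 × 2981 = 3151 days. Stroke: 0.494 × 2981 + 0.506 × 2796 = 2887 days.
- IRR ρ = 1.3, alpha 0.05.

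**Assumptions.** Two-sided alpha and these mean observation times; the article gives neither for its power calculation.

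**Formula** (self-controlled case series, signed-root likelihood ratio), with r = window length / observation length:
- π = ρr / (ρr + 1 − r)
- A = 2[π ln ρ − ln(ρr + 1 − r)]
- B = (ln ρ)² π(1 − π) / A
- power = Φ[(√(nA) − 1.96) / √B]

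**The article's own figure, one 90-day window**
- MI: r = 90/3151 = 0.02857, π = 0.03682, A = 0.002254, B = 1.083, √(nA) = 3.412. Power = Φ(1.396) = 91.9%.
- Stroke: r = 90/2887 = 0.03117, π = 0.04015, A = 0.002450, B = 1.0825, √(nA) = 3.775. Power = Φ(1.744) = 95.9%.
- With the full 4018-day study period as observation, the figures are 84.9% and 88.7%.

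The stated 90% is therefore about right for a 90-day window.

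**The same formula for each window** (MI / stroke)

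| Window | Days | Events expected under the null (n × r) | Power at IRR 1.3 | IRR detectable with 90% power |
|---|---|---|---|---|
| 0–90 | 91 | 149 / 183 | 92% / 96% | 1.29 / 1.26 |
| 1–7 | 7 | 11.5 / 14.1 | 17% / 20% | 2.17 / 2.03 |
| 8–14 | 7 | 11.5 / 14.1 | 17% / 20% | 2.17 / 2.03 |
| 15–28 | 14 | 23.0 / 28.2 | 29% / 34% | 1.78 / 1.70 |
| 29–90 | 62 | 102 / 125 | 80% / 87% | 1.35 / 1.31 |

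Worked example, MI in a 7-day window: r = 7/3151 = 0.002222, A = 0.000182, B = 1.089, √(nA) = 0.970. Power = Φ(−0.949) = 17%.

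**Day 0**
- The listed windows cover 7 + 7 + 14 + 62 = 90 days, numbered 1 to 90. A period of 0–90 has 91 days. The missing day is day 0.
- Under the null, chance alone would put about 5165.6/3151 = 1.6 MIs and 5814.6/2887 = 2.0 strokes on that day. A same-day cluster would stand out against this, but the article gives no count.

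**Baseline**
- With one UTI, time outside the risk period averages 3151 − 91 = 3060 days for MI. The prerisk week is 7/3060 = 0.23% of it. The two definitions therefore differ little in person-time, and matter only if events cluster strongly in that week.

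**The case against.** **An overall estimate is planned.** The general sentence in Statistical analysis covers risk periods against baseline, Exposure defines the risk period as 0–90 days, and objective 1 commits to a 90-day IRR. A reader might infer that nothing planned tests the hypothesis, or that the powered estimate will never be produced. The documents do not support that: the four windows can be read as additions. What remains is that no sentence names the overall IRR as primary.

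**Day 0 is not baseline under the plan's own rules.** Study design and Exposure place it in the risk period. This stands. It would be dropped, or left in baseline against those rules, only if the windows were coded literally as listed. The labels might instead count the UTI date as day 1, since they sum to 90; but the article does not say so, and the last of the 91 days would then have no window.

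**Nobody claimed power for the sub-windows.** True. The 1.3 figure is tied to 90 days and is not an error. The sub-window figures only show that it cannot be borrowed if a short window becomes the headline. They also depend on a 10% exposure share that the article calls conservative.

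**Multiplicity.** A reader might treat four windows by two outcomes as eight tests and work out a familywise error rate. That needs a rule that any one of them confirms the hypothesis, and independent tests. The plan states no such rule, and the windows share one baseline, so I give no such figure.

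**A condensed article leaves detail to a fuller document.** This is a fair defence against missing detail. Here, however, the article does state its windows and two baseline definitions, and they do not agree with its other rules.

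**Conclusion.** The concern holds in a limited form. The hypothesis, objective 1 and the power figure agree on a 90-day (0–90) contrast. The specific reporting sentence does not name that contrast as primary, omits day 0, and sits beside two definitions of baseline.

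On size: the power of 92% (MI) and 96% (stroke) at IRR 1.3 over 90 days falls to 17–20% in each 7-day window, 29–34% in days 15–28 and 80–87% in days 29–90. These figures assume 10% exposed, two-sided alpha and the article's mean observation times. The effect of day 0 on the estimates cannot be sized from the article. The baseline discrepancy is probably small.

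This should be settled before the analysis is run, but it does not invalidate the design or the power calculation, and it ranks below a must-fix.

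**What to change.** - In Statistical analysis, name the adjusted IRR over the whole 0–90-day risk period as the primary estimate, one for MI and one for stroke. Label the four windows secondary.
- Assign day 0 explicitly to the risk period, either inside the first window (0–7) or as its own stratum, and never to baseline. Add a sensitivity estimate of the overall IRR that excludes day 0.
- In objective 1, use the Study design definition of baseline: time outside both the risk and the prerisk periods.
- In Sample size and power, state that the 90% applies to the 90-day contrast only.

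Cost: wording, one extra model per outcome and the day-0 sensitivity run, all on data already held. Power for the primary contrast is unchanged (92% and 96% with day 0 included, on the same assumptions).
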